**Principal Investigator Signature and Contact Information**

**Principal Investigator (print)**

**Principal Investigator (signature)**

**Date of Signature**

**Institution/Affiliation**

**City, Province, Country**

# Study Synopsis

| **Study title** | A prospective, open-label, multicenter, randomized, phase 3 study to assess the efficacy and tolerability of sorafenib as maintenance therapy in FLT3 internal tandem duplication (FLT3-ITD) acute myeloid leukemia (AML) undergoing allogeneic hematopoietic stem cell transplantation (allo-HSCT) |
| --- | --- |
| **Protocol number** | NFEC-2015-049 |
| **Indication** | FLT3-ITD AML undergoing first allo-HSCT |
| **Study phase** | 3 |
| **Study applicant** | Nanfang Hospital, Southern Medical University |
| **Study centers** | 7 study centers (Nanfang Hospital, Peking University People's Hospital, Xiangya Hospital, Zhujiang Hospital, Third Affiliated Hospital of Sun Yat-Sen University, First People’s Hospital of Chenzhou, First Affiliated Hospital of Guangzhou Medical University) |
| **Number of subjects planned** | Approximately 194 subjects (97 each group) will be randomized. |
| **Study duration** | Estimated to be 3 years |
| **Objectives** | **Primary objective:**  To compare the 1-year cumulative incidence of relapse in patients with FLT3-ITD AML undergoing allo-HSCT who receive sorafenib maintenance versus non-maintenance post-transplantation.  **Secondary objectives:**  To compare overall survival (OS), leukemia-free survival (LFS) and adverse effects (AEs) in patients with FLT3-ITD AML undergoing allo-HSCT who receive sorafenib maintenance versus non-maintenance post-transplantation. |
| **Study design** | This is a prospective, open-label, multicenter, randomized, phase 3 study comparing sorafenib maintenance with non-maintenance post-transplantation for patients with FLT3-ITD AML undergoing allo-HSCT. Approximately 194 subjects will be randomized in a 1:1 ratio to receive sorafenib maintenance (97 subjects) or non-maintenance (97 subjects) post-transplantation. Randomization is done with permuted blocks (block size four), and implemented through an interactive web-based response system.  **Sorafenib Group:** Sorafenib maintenance (Sorafenib is administrated at 30-60 days post-transplantation and continued until day +180).  **Control Group:** Non-maintenance (Neither sorafenib nor other FLT3 inhibitors are used post-transplantation).  Disease assessment including routine blood and bone marrow (BM) assessment will be regularly performed post-transplantation. BM assessment, including BM smear and FLT3-ITD mutation is performed before randomization, every month for the first three months after enrollment, every two months from the 4th to 9th month after enrollment, and then every three months until the study is completed.  All subjects will be followed for safety and tolerability within 210 days post-transplantation. With the exception of graft-versus-host disease (GVHD) and hematologic AEs, all AEs are graded according to CTCAE version 4.0. Acute GVHD (aGVHD), chronic GVHD (cGVHD) and hematologic AEs are graded as AEs according to our self-defined criteria. |
| **Inclusion criteria** | Subjects eligible for enrolment in this study must meet all of the following criteria:   1. Patients with FLT3-ITD AML undergoing first allo-HSCT 2. Age 18 to 60 years old with Eastern Cooperative Oncology Group (ECOG) performance status 0-2 3. Composite complete remission (CRc) before and after allo-HSCT (CRc must be confirmed by BM analysis within 3 days before randomization)  - CRc comprises complete remission (CR), CR with incomplete platelet recovery (CRp), and CR with incomplete hematologic recovery (CRi). - CR is defined as bone marrow (BM) blasts <5%; absence of circulating blasts and blasts with Auer rods; absence of extramedullary disease; absolute neutrophil count (ANC) ≥1·0×10^9^/L and platelet count (PLT) ≥100×10^9^/L. - CRp is defined as all CR criteria except for incomplete platelet recovery (<100×10^9^/L). - CRi is defined as all CR criteria except for incomplete hematologic recovery with residual neutropenia <1·0×10^9^/L and/ or thrombocytopenia <100×10^9^/L.  1. Hematopoietic recovery within 60 days post-transplantation  - Hematopoietic recovery post-transplantation is defined as an ANC ≥ 1.0 × 10^9^/L and a non-transfused PLT ≥ 30 × 10^9^/L within three days.  1. Sign informed consent form, have the ability to comply with study and follow-up procedures |
| **Exclusion criteria** | Subjects meeting any of the following criteria are ineligible for this study:   1. Acute promyelocytic leukemia (AML subtype M3) 2. Intolerance to sorafenib pre-transplantation 3. Life expectancy less than 30 days post-transplantation 4. Active aGVHD or uncontrolled infections within 60 days post-transplantation 5. Cardiac dysfunction (particularly congestive heart failure, unstable coronary artery disease and serious cardiac ventricular arrhythmias requiring antiarrhythmic therapy) 6. Respiratory failure ( PaO2 ≤60mmHg) 7. Hepatic abnormalities (total bilirubin ≥2 times the upper limit of normal [ULN], alanine aminotransferase or aspartate aminotransferase ≥2 times the ULN) 8. Renal dysfunction (creatinine ≥2 times the ULN or creatinine clearance rate < 30 mL/min) 9. ECOG performance status 3, 4 or 5 10. With any conditions not suitable for the trial (investigators' decision) |
| **Study treatment** | **Sorafenib maintenance**  For subjects randomized to sorafenib maintenance (sorafenib group), sorafenib is started from day +30 until day +180 post-transplantation if patients meet the inclusion criterion on day +30. For patients who do not meet the inclusion criterion on day +30 but who do so within 31-60 days post-transplantation, sorafenib is administrated at 31-60 days post-transplantation and continued until day +180. The initial dose of sorafenib is 400 mg orally twice daily (BID). In cases of grade 3 or worse AEs, dose modifications including dose reductions or interruptions are allowed at the investigator’s discretion. After the resolution of AEs, the dose is re-escalated from 200 mg once every day or 200 mg BID to 400 mg BID.  **Non-maintenance**  For subjects randomized to non-maintenance (control group), neither sorafenib nor other FLT3 inhibitors are used unless the patients experience relapse. |
| **Sample size determination** | This trial is designed to test the hypothesis that sorafenib maintenance post-transplantation is superior to non-maintenance post-transplantation with respect to relapse. The sample size calculation is based on the primary endpoint, the 1-year cumulative incidence of relapse, which is approximately 40% in the patients with FLT3-ITD AML undergoing allo-HSCT with non-maintenance post-transplantation. To identify a 20% absolute decrease in the 1-year cumulative incidence of relapse with sorafenib maintenance post-transplantation, a minimum of 176 patients (88 in each group) is required to provide the study with a significance level of 0.05 and a power of 90%. After adjusting for a 10% dropout, the total planned sample size is 194 patients (97 in each group). |
| **Statistical analysis** | Statistical analysis is performed based on the intent-to-treat (ITT) population, which includes all randomized subjects.  **Primary Efficacy Analysis:**  The primary endpoint of this study is the 1-year cumulative incidence of relapse post-transplantation, which is calculated by accounting for competing risk. Non-relapse mortality is considered a competing risk for relapse. The comparison of the cumulative incidence of relapse is tested using Fine and Gray model.   - Relapse is defined as reappearance of leukemic blasts in the peripheral blood or ≥ 5% blasts in the BM as pirate or biopsy not attributable to any other cause or reappearance or new appearance of extramedullary leukemia.   **Secondary Efficacy Analysis:**  The secondary endpoints of OS and LFS are estimated using the Kaplan-Meier method and compared using the log-rank test.   - OS is defined as the time from transplantation until death from any cause. - LFS is defined as survival in continuous CR without relapse, and refer to the time from transplantation until relapse or death from any cause.   **Safety Analysis:**  Safety and tolerability will be assessed by incidence and severity of AEs and changes from baseline of all relevant parameters, including laboratory test values, physical examination, vital signs, and ECOG performance scores. With the exception of GVHD and hematologic AEs, all AEs are graded according to CTCAE version 4.0. aGVHD, cGVHD and hematologic AEs are graded as AEs according to our self-defined criteria. All subjects will be monitored for AEs within 210 days post-transplantation. |
|  |  |

**Abbreviations**

| ADL | Activities of Daily Living |
| --- | --- |
| AE | Adverse Event |
| aGVHD | Acute Graft-versus-Host Disease |
| Allo-HSCT | Allogeneic Hematopoietic Stem Cell Transplantation |
| ALT | Alanine Aminotransferase |
| AML | Acute Myeloid Leukemia |
| AST | Aspartate Aminotransferase |
| BID | Twice Daily |
| BM | Bone Marrow |
| cGVHD | Chronic Graft-versus-Host Disease |
| CR | Complete Remission |
| CRF | Case Report Form |
| CTCAE | Common Terminology Criteria for Adverse Events |
| ECOG | Eastern Cooperative Oncology Group |
| FLT3-ITD | FMS-Like Tyrosine Kinase 3-Internal Tandem Duplication |
| GCP | Good Clinical Practice |
| GVHD | Graft-versus-Host Disease |
| ITT | Intent-To-Treat |
| LFS | Leukemia-Free Survival |
| NIH | National Institutes of Health |
| NR | No Evidence of Response |
| OS | Overall Survival |
| PB | Peripheral Blood |
| PDGF | Platelet-Derived Growth Factor |
| PR | Partial Remission |
| QD | Once Every Day |
| SAE | Serious Adverse Event |
| TKD | Tyrosine Kinase Domain |
| ULN | Upper Limit of Normal |
| VEGF | Vascular Endothelial Growth Factor |

# 1. Introduction

Acute myeloid leukemia (AML) is a heterogeneous tumor derived from hematopoietic stem cells with a series of cytogenetic, genetic, and epigenetic abnormalities.[^1^](#_ENREF_1) FMS-like tyrosine kinase 3 (FLT3) gene mutations represent one of the most frequent genetic alterations in AML, with an incidence of approximately 30%.[^2^](#_ENREF_2) There are two categories of FLT3 mutations: internal tandem duplication (ITD) occurring in the juxtamembrane domain of the receptor (FLT3-ITD, approximately 25%) and point mutations resulting in single amino acid substitutions in the activation loop of the tyrosine kinase domain (FLT3-TKD, approximately 5%-7%).[^2^](#_ENREF_2) Patients with FLT3-ITD AML usually have a worse prognosis than those with wild-type FLT3 AML due to shorter remission duration and higher relapse, and these patients are rarely cured by chemotherapy alone.[^3^](#_ENREF_3)^,^ [^4^](#_ENREF_4) Allogeneic hematopoietic stem cell transplantation (allo-HSCT) can improve the outcomes of these patients, but the leukemia relapse rate remains high.[^5^](#_ENREF_5)^,^ [^6^](#_ENREF_6)

FLT3-ITD mutations can render the tyrosine kinase constitutively active and thus result in chronic stimulation of downstream signaling pathways and abnormal proliferation of leukemic cells.[^7^](#_ENREF_7) Inhibition of activated FLT3-ITD is an important therapeutic strategy to treat the active disease and prevent relapse. Sorafenib is a multi-kinase inhibitor that blocks multiple pathways involved in the development and progression of AML, such as FLT3-ITD, Ras/Raf, as well as vascular endothelial growth factor (VEGF) and platelet-derived growth factor (PDGF) receptors.[^7^](#_ENREF_7)^,^ [^8^](#_ENREF_8) A growing body of studies has demonstrated that the addition of sorafenib to chemotherapy could prolong the remission duration of FLT3-ITD AML.[^9-11^](#_ENREF_9) A phase I trial reported that sorafenib maintenance post-transplantation was safe for patients with FLT3-ITD AML undergoing allo-HSCT.[^12^](#_ENREF_12) Several retrospective studies suggested that sorafenib maintenance post-transplantation might reduce relapse and improve survival. [^13^](#_ENREF_13)^,^ [^14^](#_ENREF_14) To date, prospective randomized study on sorafenib as maintenance therapy post-transplantation is lacking. Therefore, we design this open-label, multicenter, randomized, phase 3 study to evaluate the efficacy and tolerability of sorafenib as maintenance therapy in patients with FLT3-ITD AML undergoing allo-HSCT.

# 2. Study objectives

## 2.1 Primary Objective

The primary objective of this study is to compare the 1-year cumulative incidence of relapse post-transplantation in patients with FLT3-ITD AML undergoing allo-HSCT who receive sorafenib maintenance versus non-maintenance post-transplantation.

## 2.2 Secondary Objectives

The secondary objectives of this study are to compare overall survival (OS), leukemia-free survival (LFS) and adverse effects (AEs) in patients with FLT3-ITD AML undergoing allo-HSCT who receive sorafenib maintenance versus non-maintenance post-transplantation.

# 3. Study Design

This is a prospective, open-label, multicenter, randomized, phase 3 study of comparison of sorafenib maintenance versus non-maintenance post-transplantation in patients with FLT3-ITD AML undergoing allo-HSCT. The study design is illustrated in Figure 1.

Subjects with FLT3-ITD AML receiving first allo-HSCT will be screened for eligibility. Medical history evaluation, vital sign, physical examination, Eastern Cooperative Oncology Group (ECOG) performance status, blood and urine sampling for laboratory tests, electrocardiogram, chest imaging examination as well as bone marrow (BM) assessment will be performed to determine study eligibility, all of which must be performed ≤3 days prior to randomization. Eligible subjects will be randomized in a 1:1 ratio to receive sorafenib maintenance or non-maintenance post-transplantation. Randomization is performed with randomization codes generated by a computer-generated randomization system.

Based on the randomization and assignment, the subjects will receive sorafenib maintenance or non-maintenance post-transplantation. For subjects in the experimental intervention arm (sorafenib group), sorafenib is started from day +30 until day +180 post-transplantation if patients meet the inclusion criterion on day +30. For patients who do not meet the inclusion criterion on day +30 but who do so within 31-60 days post-transplantation, sorafenib is administrated at 31-60 days post-transplantation and continued until day +180. The initial dose of sorafenib is 400 mg orally twice daily (BID). In cases of grade 3 or worse AEs, dose modifications including dose reductions or interruptions are allowed at the investigator’s discretion. After the resolution of AEs, the dose is re-escalated from 200 mg once every day (QD) or 200 mg BID to 400 mg BID at the discretion of the investigator. For subjects in the no intervention arm (non-maintenance, control group), neither sorafenib nor other FLT3 inhibitors are used unless the patients experience relapse. No crossover between the two groups before relapse will be allowed.

Disease assessment including routine blood and BM assessment will be regularly performed post-transplantation. BM assessment, including BM smear and FLT3-ITD mutation is performed before randomization, every month for the first three months after enrollment, every two months from the 4th to 9th month after enrollment, and then every three months until the study is completed.

All subjects will be followed for safety and tolerability within 210 days post-transplantation. With the exception of graft-versus-host disease (GVHD) and hematologic AEs, all AEs are graded according to CTCAE version 4.0. Acute GVHD (aGVHD), chronic GVHD (cGVHD) and hematologic AEs are graded as AEs according to our self-defined criteria.

**
[figure not shown]
Figure 1 Study Schema**

FLT3-ITD= FLT3 internal tandem duplication; AML= acute myeloid leukemia; allo-HSCT= allogeneic hematopoietic stem cell transplantation; ECOG= Eastern Cooperative Oncology Group; OS= overall survival; LFS= leukemia-free survival; AEs= adverse effects.

# 4. Subject Selection Criteria

## 4.1 Subject Selection Criteria

### 4.1.1 Number of Subjects

Approximately 194 subjects will be randomized to sorafenib or control group (97 subjects per group).

### 4.1.2 Inclusion Criteria

Subjects eligible for enrolment in this study must meet all of the following criteria:

1. Patients with FLT3-ITD AML undergoing first allo-HSCT

2. Age 18 to 60 years old with ECOG performance status 0-2

3. Composite complete remission (CRc) before and after allo-HSCT (CRc must be confirmed by BM analysis within 3 days before randomization).

- CRc comprises complete remission (CR), CR with incomplete platelet recovery (CRp), and CR with incomplete hematologic recovery (CRi).
- CR is defined as one marrow (BM) blasts <5%; absence of circulating blasts and blasts with Auer rods; absence of extramedullary disease; absolute neutrophil count (ANC) ≥1·0×10^9^/L and platelet count (PLT) ≥100×10^9^/L.
- CRp is defined as all CR criteria except for incomplete platelet recovery (<100×10^9^/L).
- CRi is defined as all CR criteria except for incomplete hematologic recovery with residual neutropenia <1·0×10^9^/L and/ or thrombocytopenia <100×10^9^/L.

4. Hematopoietic recovery within 60 days post-transplantation

- Hematopoietic recovery post-transplantation is defined as an ANC ≥ 1.0 × 10^9^/L and a non-transfused PLT ≥ 30 × 10^9^/L within three days.

5. Sign informed consent form, have the ability to comply with study and follow-up procedures

### 4.1.3 Exclusion Criteria

Subjects meeting any of the following criteria are ineligible for this study:

1. Acute promyelocytic leukemia (AML subtype M3)

2. Intolerance to sorafenib pre-transplantation

3. Life expectancy less than 30 days post-transplantation

4. Active aGVHD or uncontrolled infections within 60 days post-transplantation

5. Cardiac dysfunction (particularly congestive heart failure, unstable coronary artery disease and serious cardiac ventricular arrhythmias requiring antiarrhythmic therapy)

6. Respiratory failure (PaO2 ≤60mmHg)

7. Hepatic abnormalities (total bilirubin ≥2 times the upper limit of normal [ULN], alanine aminotransferase [ALT] or aspartate aminotransferase [AST] ≥2 times the ULN)

8. Renal dysfunction (creatinine ≥2 times the ULN or creatinine clearance rate < 30 mL/min)

9. ECOG performance status 3, 4 or 5

10. With any conditions not suitable for the trial (investigators' decision)

## 4.2. Withdrawal Criteria

Subjects are free to withdraw consent and discontinue participation in the study at any time and without prejudice to future treatment. A subject's participation in the study may be discontinued at any time at the investigator's discretion. Justifiable reasons for a subject to be withdrawn from the study include:

1. Inability to fully comply with the study protocol

2. Initiation of alternative treatment of other FLT3 inhibitors post-transplantation

3. Unacceptable toxicity

4. Best interest of the subject based upon the investigator’s discretion

5. At the request of the study subject at any time and for any reason

Subjects will be followed up unless the informed consent is withdrawn. The reason for withdrawal from study participation and the date must be documented in the case report form (CRF). The investigator must complete the last visit, including vital signs, physical examination, laboratory tests, disease status and AE assessment, all of which must be documented in the CRF.

# 5. Study Procedures

## 5.1 Screening

Subjects with FLT3-ITD AML receiving first allo-HSCT will be screened for eligibility. Medical history evaluation, vital sign, physical examination, ECOG performance status, blood and urine sampling for laboratory tests, electrocardiogram, chest imaging examination as well as BM assessment will be performed to determine study eligibility, all of which must be performed ≤3 days prior to randomization.

## 5.2 Treatment Allocation and Blinding

This is an open-label study. Neither subjects nor investigators will be blinded to treatment. Upon completion of all the required screening assessments, eligible subjects will be randomized at 1:1 ratio to receive sorafenib maintenance or non-maintenance post-transplantation. Randomization is done with permuted blocks (block size four), and implemented through an interactive web-based response system.

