## 5.3 Study Treatment

## 5.3.1 Sorafenib Group (sorafenib maintenance therapy)

Sorafenib is started from day +30 until day +180 post-transplantation if patients meet the inclusion criterion on day +30. For patients who do not meet the inclusion criterion on day +30 but who do so within 31-60 days post-transplantation, sorafenib is administrated at 31-60 days post-transplantation and continued until day +180. The initial dose of sorafenib is 400 mg orally BID. In cases of grade 3 or worse AEs, dose modifications including dose reductions or interruptions are allowed at the investigator’s discretion. After the resolution of AEs, the dose is re-escalated from 200 mg QD or 200 mg BID to 400 mg BID at the discretion of the investigator.

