# 12. Materials for the Study

All materials provided to study sites and investigators are as follows:

- The study protocol
- Informed consent
- CRF

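### The protocol discloses a single fixed block size of four in an open-label trial, so between about 1% and 33% of allocations could be known in advance, depending on a list structure it does not state

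*Protocol*

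**What the plan says.** Section 5.2 of the protocol fixes the method: "Randomization is done with permuted blocks (block size four), and implemented through an interactive web-based response system". The synopsis gives the same block size. The ratio is equal ("eligible subjects will be randomized at 1:1 ratio to receive sorafenib maintenance or non-maintenance post-transplantation"), so each block holds two patients per arm. The same section says "Neither subjects nor investigators will be blinded to treatment". Section 12 opens with "All materials provided to study sites and investigators are as follows", and the protocol is the first item listed.

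The synopsis names "7 study centers". Neither it, section 3 nor section 5.2 names a stratification factor, mentions varied or concealed block sizes, or says whether each centre has its own blocks or all centres draw from one list.

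On entry, section 4.1.3 ends with an open exclusion, "With any conditions not suitable for the trial", left to the investigator. Section 5.3.1 provides for a later start: "For patients who do not meet the inclusion criterion on day +30 but who do so within 31-60 days post-transplantation".

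**The concern.** The people who enrol patients know the block length and see the treatment of their own earlier patients. Once both places for one arm in a block have been used, the rest of the block is certain. The web system hides the list, but it cannot stop this deduction.

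A prediction matters only if it can be acted on, and there is some room for that. Exclusion 10 is open-ended. Other criteria in section 4.1.3 call for judgement, such as active acute GVHD, uncontrolled infection and life expectancy. The investigator also schedules screening, which section 5.1 places within 3 days before randomisation.

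If patients at higher or lower risk of relapse were held back or brought forward according to the expected arm, the arms would differ in prognosis at entry. The primary endpoint, 1-year cumulative incidence of relapse, could then be biased. Analysing all randomised patients as assigned (section 11.3.1) does not repair this, because the selection happens before randomisation.

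**Working it through.** The protocol gives no predictability figure, so there is none to reproduce.

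**Inputs.** Block size 4, ratio 1:1 and open-label treatment (section 5.2); seven centres and 194 patients (synopsis). Centre shares are not given and are assumed below.

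**Step 1: an observer who sees the whole block.** With arms A and B there are six equally likely blocks, so 6 × 4 = 24 positions. A position is certain when one arm's two places are already used. The guesser names the arm that is behind and scores one half when the arms are level.

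| Blocks | Certain positions per block | Expected correct guesses per block |
|---|---|---|
| AABB, BBAA | 2 | 0.5 + 0 + 1 + 1 = 2.5 |
| ABAB, ABBA, BABA, BAAB | 1 | 0.5 + 1 + 0.5 + 1 = 3 |

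- Certain: (2 × 2 + 4 × 1) / 24 = 8/24 = 33.3%, or about 194 / 3 ≈ 65 patients. Within one block the share is 25% or 50%.
- Correct guesses: (2 × 2.5 + 4 × 3) / 24 = 17/24 = 70.8%, against 50% by chance.

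**Step 2: how much of the block a centre sees.** Simulation with 194 patients and seven centres:

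| List structure | Certain allocations |
|---|---|
| Blocks within centre | about 32% (last blocks may be incomplete) |
| One central list, allocations shared between centres | 33.3% |
| One central list, own patients only, equal centres | about 0.7% |
| One central list, own patients only, one centre enrols 60% | about 7% |

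The last two rows let a centre know where each block begins, which it usually would not, so they are if anything too high. In those two settings a centre that guesses from its own running imbalance is right 51–52% of the time.

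**Step 3: effect of varied sizes.** Sizes 4, 6 and 8 are drawn at random, and the observer sees every allocation in the sequence:

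- Certain predictions fall to about 2%, even if the observer knows the set of possible sizes and tracks every block boundary consistent with the sequence.
- Correct guesses on imbalance fall only to about 68%.
- A longer fixed and known size would help less: 25% certain with blocks of six and 20% with blocks of eight.

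**The case against.** The strongest reply is that one third depends on a condition the protocol does not state. It names no stratification by centre and describes a single web-based system, which may well mean one list for all seven centres. Predictability is then close to chance. This stands: one third is a ceiling, and a reader should not infer that a third of this trial's allocations are known to the centres. Nor does the text say that a centre sees other centres' assignments; being unblinded covers a centre's own patients. But a central list is not stated either, so the low figure cannot be assumed.

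A reader might also infer a free 30-day window for choosing when to randomise. The text does not give one. Days 31–60 are for patients who do not meet the criterion on day +30, and delaying a patient already screened could mean repeating tests that must fall within 3 days of randomisation. What remains is exclusion 10, a common catch-all, together with the criteria that need judgement and some control over scheduling.

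Fixed blocks of four are a legitimate method, and the sections that describe them agree. Nothing shows that enrolment has been or would be steered, and no bias in relapse incidence has been estimated. The supportable word is that bias could arise.

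The blinded panel in section 14 does not answer the point, since it is described as monitoring and not as controlling enrolment.

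**Conclusion.** The point holds as an avoidable weakness in allocation concealment, not as an error or a contradiction. With the block size disclosed and treatment open, the share of allocations that a centre could know in advance lies between about 1% and 33%.

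The upper end needs blocks within centre or centres sharing allocations. The lower end needs one central list with each centre seeing only its own patients and equal centre sizes; one dominant centre with an assumed 60% of patients raises it to about 7%. The protocol leaves open which applies.

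The point is minor. It is worth raising because the change is almost free and selection before randomisation cannot be corrected in the analysis. The planned sample size is not affected.

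**What to change.** 1. Set the web system to draw block sizes at random, for example 4, 6 and 8.
2. Delete the block size from the synopsis and section 5.2, and record the sizes in a randomisation document that enrolling staff cannot see.
3. State in section 5.2 whether blocks run per centre or from one central list. That sentence settles where in the 1% to 33% range the present design lies, and it can be written without revealing block sizes.

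If blocks run within centre, steps 1 and 2 remove most certain predictions (33% to about 2%) but leave guessing on imbalance at about 68%. Under a central list, guessing stays at about 51–52% with or without varied sizes, so the gain there is small.

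The cost is one system setting, a deleted phrase and an added sentence, with a slightly larger possible difference in arm sizes (a few patients). If recruitment has begun, the change still protects the remaining allocations.
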